## Methods

### Study Design

This is a randomized, placebo-controlled, double-blind, crossover trial (Figure 1). Participants are assigned in a 1:1 ratio to 2 treatment periods, each lasting 1 hour, with a 1-week washout period between them.

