### Experimental Design

Patients will be evaluated on 3 nonconsecutive days. Clinical data (anthropometrical and bronchiectasis severity assessed by FACED [FEV1% predicted score, Age, Chronic colonization by *Pseudomonas aeruginosa*, Radiological extension, Dyspnea]) [10] will be obtained from the participants’ medical records. On day 1, pulmonary function will be assessed via whole-body plethysmography, and the maximal exercise capacity will be measured via a cardiopulmonary exercise test (CPET) to obtain the peak work rate (W_peak_). On day 2, patients will be randomly allocated to receive BDs (160 µg of ipratropium bromide and 400 µg of fenoterol hydrobromide) or a placebo (norflurane or HFA134A, a harmless propellant), followed by simultaneous assessments of endurance exercise capacity (constant work-rate exercise test, CWRET) and thoracoabdominal kinematics (optoelectronic plethysmography). On day 3, after at least 1-week washout with no maximum deadline, the patient will repeat the same assessment as on day 2 in the reverse order. This washout period was defined according to the maximum BD withholding time (48 hours) [22], aiming to minimize the carryover effect. In case of NCFB exacerbation during the washout period, a 30-day recovery interval will be performed for the next assessment. Spirometric evaluations will be performed pre-CWRET before and after BDs or placebo. The time to the limit of tolerance (T_lim_) will be obtained under both conditions (BDs and placebo). Thoracoabdominal kinematics will be assessed at 3 time points: at rest (T1), during the unloaded exercise (T2), and at 75% W_peak_ obtained from CPET (T3). Thoracoabdominal kinematics will assess volume variables, including total chest wall volume, compartmental volume, and TAA. The assessor and patient will be blinded to the intervention (BDs or placebo). All exercise tests will be performed on a cycle ergometer (Figure 2).

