### Data Analysis

A sample of 39 participants was estimated as the number needed to provide 80% power to detect a between-group difference of 55.2 (SD 119.4) seconds in T_lim_, according to a pilot study (n=10; 80% females; 47.90 [SD 10.95]; FEV1 57.25% [SD 35.08%] predicted; FVC 69.12% [SD 31.21%] predicted; residual volume/total lung capacity 196% [SD 18.01%] predicted). The final sample size will be set at 45 patients, assuming up to a 10% loss during follow-up. The results will be analyzed according to the intention-to-treat principle to preserve the effects of group allocation and to provide an assessment of the practical impact of the intervention [38], as recommended by the CONSORT (Consolidated Standards of Reporting Trials) statement [39] (Multimedia Appendix 1). A median substitution will be imputed with the missing data. Data distribution will be assessed via the Kolmogorov‒Smirnov test. Comparisons between BDs and placebo data will be analyzed via 1-sided *t* tests or Wilcoxon tests for T_lim_ and repeated-measures analysis of variance or Friedman tests for thoracoabdominal kinematics variables. The number of participants who achieved the minimum clinically important difference (>60 seconds) in CWRET between BDs and placebo will be compared via chi-square tests. Pearson or Spearman correlation will be used to verify the associations between CWRET and thoracoabdominal kinematics variables. *P* values <.05 indicate statistical significance. The carryover, period, and sequence effects for T_lim_ will be estimated using generalized estimating equations models. If the carryover effect is not significant, a reduced model excluding the carryover term will be refitted. The statistical analysis will be performed using SPSS software (version 17.0; IBM Corp).

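### The carryover and sequence effects for T_lim cannot both be estimated in this two-period crossover, and the rule that drops carryover only when it is not significant is a pretest that distorts the GEE treatment test

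*Protocol article*

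**What the plan says.** The Study Design section describes a two-period crossover: "Participants are assigned in a 1:1 ratio to 2 treatment periods, each lasting 1 hour, with a 1-week washout period between them". Under Experimental Design, on day 3 "the patient will repeat the same assessment as on day 2 in the reverse order". Each patient therefore contributes one T_lim on bronchodilator and one on placebo, in one of two orders.

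The Data Analysis section gives the treatment comparison first: "Comparisons between BDs and placebo data will be analyzed via 1-sided *t* tests or Wilcoxon tests for T_lim". It later adds a model: "The carryover, period, and sequence effects for T_lim_ will be estimated using generalized estimating equations models". The selection rule follows: "If the carryover effect is not significant, a reduced model excluding the carryover term will be refitted". Only one significance level, 5%, is stated for the whole analysis. The section does not say how the GEE result relates to the t or Wilcoxon test.

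Experimental Design already deals with carryover by design: the washout is at least one week, set against a longest bronchodilator withholding time of 48 hours.

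**The concern.** There are two faults in the same two sentences.

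First, a two-sequence, two-period design cannot tell carryover from a difference between the sequence groups. Both show up as a difference in the patients' totals over the two periods. A model that contains both has no unique solution, so the carryover P value on which the rule depends is undefined until one of the two terms is removed. The article does not say which.

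Second, if the analyst removes sequence so that carryover can be tested, the rule becomes the two-stage procedure. A significant carryover term stays in the model, and the treatment coefficient is then the period-1 comparison between groups. That comparison is strongly correlated with the carryover test that selected it. At stake are the error rate of a treatment effect read from the GEE and, in trials where the pretest is significant, the within-patient precision for which the crossover was chosen.

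**Working it through.** **Inputs.** From Data Analysis: difference 55.2 s, SD 119.4 s, 80% power, 39 participants, 5% level. From Study Design and Experimental Design: two sequences in a 1:1 ratio, two periods, one T_lim per period. Assumed: within-patient correlation ρ of T_lim from 0.3 to 0.9, normal data, pretest at 5%, and 19 per sequence (38 patients, the nearest even split to 39).

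**1. The plan's own figure.** A paired t test with 55.2/119.4 = 0.462 needs n = 39 at two-sided 5% (power 0.803). At one-sided 5% it needs 31. The stated 39 is therefore reproduced when 119.4 s is the SD of the paired difference, and that reading is used below.

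**2. Aliasing.** Code treatment 1 = bronchodilator, period 1 = second, sequence 1 = placebo first, carryover 1 = placebo after bronchodilator.

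| Cell | Intercept | Period | Treatment | Sequence | Carryover |
|---|---|---|---|---|---|
| BD first, period 1 | 1 | 0 | 1 | 0 | 0 |
| BD first, period 2 | 1 | 1 | 0 | 0 | 1 |
| Placebo first, period 1 | 1 | 0 | 0 | 1 | 0 |
| Placebo first, period 2 | 1 | 1 | 1 | 1 | 0 |

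In every row, carryover = (1 + period − treatment − sequence)/2. Five columns have rank 4; dropping either sequence or carryover leaves rank 4. GEE changes how the variance is estimated, not the rank of the mean model. Experimental Design schedules only spirometry before dosing on each test day. The CWRET Analysis section mentions a baseline T_lim for setting the work rate, but Data Analysis does not bring it into the model.

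**3. Precision of the two possible treatment contrasts.**

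Within-patient, adjusted for period: SE = (119.4/2) × √(1/19 + 1/19) = 59.7 × 0.3244 = 19.4 s.

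Period 1 only (carryover kept, sequence omitted): SD of one T_lim σ = 119.4/√(2(1 − ρ)), SE = σ × 0.3244. Its correlation with the carryover contrast is √((1 + ρ)/2).

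| ρ | σ (s) | SE, period 1 (s) | Correlation with pretest |
|---|---|---|---|
| 0.3 | 100.9 | 32.7 | 0.81 |
| 0.5 | 119.4 | 38.7 | 0.87 |
| 0.7 | 154.1 | 50.0 | 0.92 |
| 0.9 | 267.0 | 86.6 | 0.97 |

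**4. Error of the two-stage rule, with no carryover and no treatment effect.** This was simulated, with t tests standing in for the GEE Wald tests. About 5% of trials have a significant pretest. In those, the period-1 test rejects falsely in about 31% to 50% (one-sided). Overall error is about 6.1% to 7.1% one-sided and 6.8% to 8.8% two-sided. A check by hand: the within-patient contrast is independent of the pretest, so one-sided error is 0.95 × 0.05 + 0.05 × 0.31 = 0.063 at the low end and 0.95 × 0.05 + 0.05 × 0.50 = 0.073 at the high end. This agrees within simulation error and rounding.

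**5. What the pretest buys.** With 39 patients and ρ from 0.5 to 0.9, a carryover as large as the whole 55.2 s effect would be detected in only 6% to 13% of trials.

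**6. Average bias and power.** After a significant pretest without true carryover, the mean period-1 estimate is about 0 s when the truth is 0, and 51 to 57 s when the truth is 55.2 s. Overall power with 39 patients falls from 0.80 to 0.79 two-sided and from 0.88 to 0.86 one-sided.

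**The case against.** The strongest reply is that the treatment test for T_lim is the one-sided t or Wilcoxon test. It carries no condition, and the Abstract lists it without mentioning GEE. The GEE sentence names carryover, period and sequence, not treatment. On that reading the GEE is a supporting check, and the decisive test keeps its 5% error; the paired t test simulated at about 5% one-sided. This stands. A reader might infer that the primary test itself is inflated, but the article does not support that. Inflation arises only for a treatment effect read from the GEE.

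The article also does not say that sequence would be the term removed. If carryover were removed instead, the model would be treatment, period and sequence, which is sound. That too is correct: the figures in step 4 describe one of two ways to resolve an inestimable model. It does not rescue the text, because the pretest rule has a meaning only if carryover is the term kept for testing.

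Three further inferences go too far. The two-sided error range is not the one to lead with, since the plan's test is one-sided. The retained estimate is not biased on average when there is no carryover; the trouble is test size and imprecision. Power does not collapse either: the period-1 comparison is weak, but without carryover it would be used in only about 5% of trials.

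**Conclusion.** The point holds in limited form and should be fixed. The aliasing is algebra and needs no assumption: as described, the model cannot be fitted with both carryover and sequence. The pretest rule is faulty. For a GEE treatment effect it raises one-sided error from 5% to about 6.1% to 7.1%, and a significant pretest replaces a standard error of about 19 s with one of 33 to 87 s. Overall power loses 1 to 2 points.

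These sizes rest on the assumed correlation, normal data, a 5% pretest, and carryover being the term retained. The conclusion that the rule is better removed does not depend on the exact correlation, since inflation appeared at every value tried. If the t or Wilcoxon test alone decides, its error rate is unaffected; this is why the point is not critical to the trial.

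**What to change.** In Data Analysis:

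- Delete the carryover term and the sentence that makes its removal depend on significance. Keep treatment, period and sequence in the GEE.
- Rest the assumption of no carryover on the washout of at least one week against the 48-hour maximum withholding time.
- State that one within-patient analysis of T_lim is decisive, whatever any carryover or sequence result shows. The named t or Wilcoxon test may serve; the defect does not require replacing it with a mixed model.
- Report the sequence contrast descriptively only, noting that it cannot be separated from carryover.

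The cost is a change of wording. No new data, visits or patients are needed. It should be settled before the data are analysed.

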## Results

This study was funded by São Paulo Research Foundation (FAPESP, grants 2018/17788-3) and Conselho Nacional de Desenvolvimento Científico e Tecnológico (grant 312.279/2018-3) for the CardioO2 system (Medical Graphics Corporation) and the optoelectronic plethysmography system, respectively. The ethics approval (3.008.886) was granted in November 2018. The pilot study commenced in April 2019 but was interrupted due to the COVID-19 pandemic in early 2020; it was restarted and completed in April 2022. As of December 2023, enrolling by invitation is the last status of Clinical Trials.gov PRS (NCT05183841). Consent was obtained from 39 patients until May 2025. Of the 39 consented patients, one was excluded due to difficulty performing the cycle ergometer test and 6 patients did not complete the protocol. Data collection is expected to continue until November 2025. Data analysis is anticipated to begin in 2025, with initial results anticipated to be reported on and published after the completion of data collection. The publication of results is anticipated to be in 2025-2026.

## Discussion

### Principal Findings and Comparison to Prior Work

This randomized, controlled, double-blind crossover trial is intended to test the effect of dual bronchodilation on the exercise capacity of individuals with NCFB. In clinical practice, BDs have been recommended to treat only symptomatic individuals with NCFB [4]. Despite the common use of BDs in this population, there are no reports of their effects on the patient’s exercise capacity. A previous study showed no difference in the 6-minute walking test results of individuals with NCFB after a 6-month BD treatment (tiotropium) compared to the control group [13]. However, the exercise capacity was not the primary end point of this trial, and the 6-minute walking test is not the most appropriate choice for evaluating that outcome.

BDs have long been recommended to reduce exercise-induced bronchoconstriction and exercise limitation in patients with asthma and COPD, respectively [7,8]. According to the Global Initiative for Chronic Obstructive Lung Disease [8], BDs are recommended for individuals with severe disease, symptoms, or exercise limitations, as BDs reduce airway resistance, promote lung deflation, and enable better alveolar ventilation at rest and during exercise. Furthermore, dual bronchodilation is associated with better physical endurance capacity, exercise capacity, and physical activity level in individuals with COPD [40]. Additionally, TAA is very prevalent in individuals with COPD and is associated with exercise limitations [15,16]. The main effect of BDs on the ventilatory capacity is an increase in basal inspiratory capacity and a reduction in dynamic hyperinflation during exercise, enhancing exercise performance [17]. Most individuals with NCFB have airflow obstruction [41], air trapping, and diffusion impairment [42,43]; however, no studies have evaluated TAA or thoracoabdominal kinematics of patients with NCFB. Extrapulmonary features such as peripheral muscle endurance, exercise capacity, and health status are also affected by NCFB [44]. Hence, it seems plausible that BDs may improve the exercise capacity of individuals with NCFB, similar to what has been observed in individuals with COPD. Therefore, we hypothesize that dual bronchodilation can improve the exercise capacity of individuals with NCFB and reduce TAA during exercise.

### Strengths and Limitations

The strengths of this study include patient randomization and the crossover design, which reduce variability and increase statistical power. Besides, this is the first study to assess the exercise capacity and thoracoabdominal kinematics simultaneously of individuals with NCFB. Taken together, the results may highlight the effect of BD on exercise capacity and clarify a possible mechanism associated with it. The main limitation of this study is that patients will be recruited from a single referral hospital, and individuals with long-term oxygen therapy will be excluded. Unfortunately, we had to exclude patients with long-term oxygen therapy because our CPET equipment does not assess oxygen consumption with supplemental oxygen use, as it requires a special component. These limitations reduce the external validity of our results.

### Future Directions and Conclusion

Clinicians and researchers agree that the effect of BD in patients with NCFB and information in this field is urgently needed. If successful, this study will demonstrate that BDs can improve the exercise capacity in adults with NCFB and reduce TAA during exercise. Since exercise capacity reflects a patient’s functional status, future studies may explore whether its optimization can enhance independence and the quality of life in this population.

## Appendix

Multimedia Appendix 1 CONSORT checklist.

## Abbreviations

BD: bronchodilator
CONSORT: Consolidated Standards of Reporting Trials
COPD: chronic obstructive pulmonary disease
CPET: cardiopulmonary exercise test
CWRET: constant work-rate exercise test
FACED: FEV1% predicted score, Age, Chronic colonization by Pseudomonas aeruginosa, Radiological extension, Dyspnea
FEV1: forced expiratory volume in the first second
FVC: forced vital capacity
NCFB: non-cystic fibrosis bronchiectasis
SpO2: peripheral oxygen saturation
TAA: thoracoabdominal asynchrony
Tlim: time to the limit of tolerance
Wpeak: peak work rate
